### Implementation framework and strategy selection

2.10

The selection of implementation science frameworks for C-COMPASS was guided by the Systematic Evaluation and Selection of Implementation Science Theories, Models and Frameworks (SELECT-IT) meta-framework, which provides a structured approach for aligning theories, models, and frameworks with study purpose.

Based on this process, three complementary frameworks were selected. The Theoretical Domains Framework (TDF) will be used to identify behavioural and contextual determinants influencing ASHA delivery. The ERIC (Expert Recommendations for Implementing Change) taxonomy will be used to specify and classify implementation strategies embedded within the intervention. Implementation outcomes will be assessed using the Proctor et al. (13) taxonomy, given its suitability for early-stage evaluations where effectiveness is not yet established.

### Implementation strategy specification

2.11

Implementation strategies embedded within C-COMPASS will be specified using the ERIC taxonomy. These include training, use of educational materials, supportive supervision, audit and feedback, and identification of local champions.

These strategies are integrated within routine health system workflows, including ASHA training, CHO-led supervision, and register-based monitoring. Their application is aligned with identified behavioural and system-level determinants and will be evaluated alongside implementation outcomes.

A detailed mapping of ERIC strategies, their operationalisation, and corresponding determinants is provided in Supplementary Table S2.

### Sample size

2.12

Enrolment estimates are derived from SHRiSTI ASHA pregnancy surveillance data which indicates a mean of 4.6 stillbirths per block per month (range: 3.4–5.6), with a seasonal peak during July–October (5.2–5.6 per block per month) *(surveyed data from SHRiSTI project)*. This pattern is consistent with published systematic review by Lakhoo et al. on heat-associated stillbirth risk in South Asian settings in 2025. As described in Section 2.1, the SHRiSTI community-based surveillance estimate of 17.2 per 1,000 total births is used for planning, as it more accurately captures the true community-level burden than the HMIS facility-based figure.. The per-block estimate from the same surveillance data is 4.6 per month and this was used as a base for sample size. The study will employ a difference-in-differences (DiD) design across four blocks (two intervention, two control). With two blocks per arm, the expected enrolment rate is approximately 9.2 women per arm per month. Over the 8-week pre-intervention period, approximately 17 women per arm are expected, and over the 26-week post-intervention period, approximately 56 women per arm are expected, yielding a total sample of approximately 146 women.

The primary outcome is mean EPDS score (continuous). Assuming a clinically meaningful difference of 3.5 points, a pooled standard deviation of 6.5, two-sided alpha of 0.05, and 80% power, a minimum of 55 women per arm in the post-intervention period is required. The expected sample size of 56 per arm provides approximately 81% power. To account for an anticipated 10% attrition rate, the post-intervention data collection period may be extended to ensure a minimum effective sample size of 56 women per arm.

A pre-specified sensitivity analysis including early neonatal deaths (<24 h) is expected to add approximately 18 cases per arm. This estimate is based on a neonatal mortality rate of ∼22 per 1,000 live births in Haryana, with approximately 25% of deaths occurring within 24 h, applied to an estimated 277 live births per block per month. This yields approximately 1.5 early neonatal deaths per block per month, resulting in ∼18 additional cases per arm over the study period. The resulting post-intervention sample of approximately 74 per arm would provide approximately 91% power.

The secondary binary outcome (EPDS ≥ 13) is not used for power calculation. At an estimated baseline prevalence of 40%, the study would have approximately 44% power to detect a 16 percentage-point reduction. This analysis is therefore exploratory, and results will be reported with 95% confidence intervals to inform future cluster-randomised trial design.

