**Methods:**

This protocol describes a quasi-experimental hybrid type I effectiveness-implementation study embedded within an ongoing implementation research project, SHRiSTI, aiming to reduce stillbirths in India. The Community Continuum of Care for Compassionate Support After Stillbirth (C-COMPASS) is a co-designed, community health worker–delivered counselling intervention for women experiencing stillbirth and early neonatal death. The intervention comprises five structured contacts: a telephonic follow-up within 72 h of discharge, and on Day 7, in-person visits on Day 14 and Day 21, and a Day 42 postpartum review, supported by a red-flag referral pathway. The study will use a quasi-experimental Difference-in-Differences (DiD) analytical design across four administrative blocks (two intervention, two control), with a pre-intervention observation period (approximately 10–12 weeks) and a post-intervention period (approximately 26 weeks). This design was chosen in place of a cluster-randomised controlled trial because block-level allocation is operationally determined within the existing SHRiSTI programme. The primary effectiveness outcome will be mean Edinburgh Postnatal Depression Scale (EPDS) score at 60 days postpartum, measured by independent assessors and analysed using a linear DiD model with block-level fixed effects. An expected sample of approximately 56 women per arm in the post-intervention period provides 81% power to detect a clinically meaningful difference of 3.5 EPDS points with a total anticipated enrolment of approximately 146 women. Secondary outcomes will include binary EPDS score thresholds, grief symptoms, functional disability, and incremental cost per woman counselled. Early neonatal deaths within 24 h will be included in a pre-specified sensitivity analysis. Implementation outcomes will be assessed using the Proctor et al. taxonomy.

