### Statistical analysis

2.13

The primary Difference-in-Differences (DiD) model will be specified as a linear regression with block fixed effects:$$EPDS=\beta_{0}+\beta_{1}(Arm)+\beta_{2}(Time)+\beta_{3}(Arm\times Time)+\gamma_{k}(Block_{k})+\epsilon$$where *Arm* (1 = intervention, 0 = control), *Time* (1 = post, 0 = pre), and the interaction term (*Arm* × *Time*) represents the DiD estimator (*β*₃). A negative *β*₃ will indicate a reduction in depressive symptoms attributable to C-COMPASS. Block fixed effects (*γ*_k_) will account for time-invariant block-level confounders, including baseline ASHA performance, population characteristics, and facility access.

The pre-specified secondary binary outcome (EPDS ≥ 13) will be analysed using a logistic DiD model with the same structure. SDS and BGQ scores will be analysed using linear DiD models with block fixed effects, while BGQ screen-positive (≥4) will be analysed using logistic DiD models. Implementation outcomes (visit completion, referral completion, and documentation completeness) will be reported as proportions with 95% confidence intervals.

Parallel trends will be assessed by comparing pre-intervention EPDS distributions across study arms and blocks, along with baseline sociodemographic characteristics (20). A maximum of one additional covariate beyond block fixed effects will be included, selected *a priori* (most likely gravida or previous stillbirth) (21). A pre-specified sensitivity analysis will replicate the primary model in an expanded population including early neonatal deaths, incorporating a perinatal loss type indicator and its interaction with the intervention effect. All analyses will be conducted using Stata version 16 or R version 4.4+.

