Several limitations must be acknowledged. The quasi-experimental DiD design, while appropriate given the operational constraints of embedding evaluation within a running programme, does not provide the causal certainty of a cluster-randomised trial. Block-level allocation is determined by programme implementation schedule rather than random assignment, and unmeasured time-varying confounders at block level, such as a community event, a local health programme, or seasonal migration patterns differentially affecting one block, cannot be fully excluded, even with block fixed effects. The pre-intervention period of approximately eight weeks is short, which limits formal statistical testing of the parallel trends' assumption; while the four-block design partially mitigates this, the concern cannot be eliminated. The primary sample of approximately 146 women is sufficient for the continuous EPDS primary outcome at 81% power but is underpowered for confirmatory testing of the binary EPDS ≥ 13 threshold, which should be interpreted as exploratory and directional. ASHAs in the intervention blocks are not blinded to the nature of the intervention, introducing the possibility of social desirability effects in self-reported implementation metrics, particularly visit completion and documentation completeness. The EPDS was originally validated for postnatal depression after live birth; while it has been used in stillbirth populations across multiple settings, its psychometric properties specifically in the context of perinatal grief in rural North India have not been formally validated, and cultural norms around mourning, including the social expectation that a bereaved woman will not laugh or plan for the future, may influence item-level responses in ways that are not fully separable from clinical depression. A residual risk of exclusion remains for women who experience stillbirth entirely outside facility or ASHA notification pathways, including those in the most geographically isolated, temporary migrants and women who relocate immediately after delivery. While the dual notification design and backup ANM pathway minimise this risk, penetration data collected during the study will allow estimation of the proportion of identifiable cases successfully enrolled, and any systematic differences between enrolled and non-enrolled women will be reported. Finally, the study is conducted in a single district in one state; while Palwal's epidemiological profile is broadly consistent with high-burden rural North Indian settings, immediate generalisability to other states and contexts should not be assumed.

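### The 81% power belongs to a post-period two-sample comparison; the difference-in-differences interaction that is the primary estimate has about 28% power with 17 pre and 56 post women per arm

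*Protocol article*

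**What the plan says.** Section 2.12 (Sample size) names the design as DiD over four blocks and gives the expected numbers: "Over the 8-week pre-intervention period, approximately 17 women per arm are expected", and about 56 per arm afterwards, 146 women in all. It then sizes the study as follows: "Assuming a clinically meaningful difference of 3.5 points, a pooled standard deviation of 6.5, two-sided alpha of 0.05, and 80% power", which leads to at least 55 women per arm in the post-intervention period. It concludes: "The expected sample size of 56 per arm provides approximately 81% power".

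Section 2.13 (Statistical analysis) fixes a different analysis: "The primary Difference-in-Differences (DiD) model will be specified as a linear regression with block fixed effects". The effect is β₃, the Arm × Time coefficient.

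The power figure is repeated as the power of the study. The Abstract says that the post-period sample "provides 81% power to detect a clinically meaningful difference of 3.5 EPDS points". Section 3.1 says: "The primary sample of approximately 146 women is sufficient for the continuous EPDS primary outcome at 81% power".

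Section 2.12 gives two further figures. For the sensitivity population with early neonatal deaths: "The resulting post-intervention sample of approximately 74 per arm would provide approximately 91% power". For EPDS ≥ 13 at 40% baseline prevalence: "the study would have approximately 44% power to detect a 16 percentage-point reduction". Section 2.13 assigns DiD models to both analyses.

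**The concern.** The sample-size calculation and the primary model do not concern the same quantity. The calculation compares two post-period means. The model compares the pre-to-post change in the intervention arm with the change in the control arm. Each woman contributes one Day 60 score after her own loss, so the pre-period women are not the post-period women, and no within-woman correlation offsets the pre-period error. With only about 17 women per arm before the intervention, that error is the larger part of the variance.

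Section 2.2 hypothesises a significant reduction, and Section 3.2 ties presentation to the state and national health authorities partly to a clinically meaningful fall in mean EPDS. If a true 3.5-point benefit reaches significance less than one time in three, a reader told that the study had 81% power could take a null result as evidence that C-COMPASS does not work.

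**Working it through.** **Inputs.** Difference 3.5, SD 6.5, two-sided α 0.05, 17 pre and 56 post women per arm (Section 2.12). Linear DiD with block fixed effects (Section 2.13). Since 146 = 2 × (17 + 56), the women in the two periods are distinct.

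**1. The protocol's own figure.**
- n per arm = 2 × (1.96 + 0.8416)² × (6.5/3.5)² = 54.1, rounded up to 55.
- With 56 per arm, SE = 6.5 × √(2/56) = 1.228, and power = Φ(3.5/1.228 − 1.96) = 81.3% (80.6% with the noncentral t).

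Both stated figures reproduce, with no pre-period term.

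**2. The interaction.**
- β₃ is a contrast of four independent cell means, so SE(β₃) = 6.5 × √(2/17 + 2/56) = 6.5 × √(0.1176 + 0.0357) = 2.545.
- The pre-period share of the variance is 0.1176/0.1533 = 77%.
- Power = Φ(3.5/2.545 − 1.96) = 28% (27.7% with the noncentral t).
- 95% CI half-width = 1.96 × 2.545 = 5.0 points.
- Difference detectable with 80% power = 2.80 × 2.545 = 7.1 points, twice the target.
- The exact least-squares variance with block fixed effects (pre-period 9/8/9/8 women, post-period 28 per block) gives SE 2.546 and power 27.9%. The block terms do not restore the post-only precision.

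**3. Length of the pre-period.** Sections 2.12 and 3.1 use eight weeks; the Abstract and Section 2.4 say 10–12 weeks. At 9.2 women per arm per month, 10–12 weeks gives about 21–25 per arm.

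| Pre-period women per arm | SE(β₃) | Power for 3.5 | 95% CI half-width | Detectable at 80% |
|---|---|---|---|---|
| 17 | 2.55 | 28% | 5.0 | 7.1 |
| 21 | 2.35 | 32% | 4.6 | 6.6 |
| 25 | 2.21 | 35% | 4.3 | 6.2 |

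Unrounded, 12 weeks is 25.5 women per arm and gives 36%.

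**4. Extending the post-period.** This is the protocol's remedy for attrition. With 17 pre-period women per arm and unlimited post-period enrolment, SE falls only to 6.5 × √(2/17) = 2.23, and power is 35%.

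**5. The other two figures.**
- *Sensitivity population.* With 74 post-period women per arm, a post-only comparison gives SE = 6.5 × √(2/74) = 1.069 and power 90.6%, which is the stated 91%. The protocol gives no pre-period count for this population. At 1.5 early neonatal deaths per block per month, eight weeks add 1.5 × 2 × 8/(52/12) ≈ 5.5 per arm, or about 22.5 in all (an extrapolation). Then SE = 6.5 × √(2/22.5 + 2/74) = 2.21 and power is about 35%.
- *EPDS ≥ 13.* 40% against 24% with 56 per arm gives 44.1% post-only. As a DiD with 40% in the other three cells, the risk-difference SE is 0.189 and power is 13.5%; the logistic interaction SE is 0.814 and power is about 15%.

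**The case against.** The strongest reply is that the protocol ties its 55 and 56 women per arm openly to the post-intervention period, so the arithmetic is right for what it describes. That stands. But the result is then presented as the power for the primary outcome, and Section 2.13 analyses that outcome with a different estimator. Both are stated in the same document, so this is not a detail left to a statistical analysis plan.

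A second reply is that adjustment might recover precision. Section 2.13 allows one covariate beyond the block effects. If the residual SD fell to 5.0 (an assumption), power would be 43%; reaching 81% would need a residual SD of about 3.15. The protocol claims no such reduction.

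Four further points have some force:

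- The 28% depends on the eight-week pre-period, which the protocol contradicts elsewhere. The range 28–36% should be given until the length is settled.
- The figures assume independent women, full follow-up and no block-by-period variation. Relaxing these lowers power. About 15 pre-period women per arm (10% attrition) gives 26%; an illustrative block-by-period SD of 1 point gives an SE of about 2.9 and power of about 23%.
- The 35% for the sensitivity population is for a pooled model. Section 2.13 adds loss type and its interaction with the intervention effect. Power is then about 34% with the indicator and that interaction alone, and returns to about 28% for stillbirth if loss type is fully interacted.
- The binary outcome is already declared exploratory, so correcting 44% changes no decision.

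Section 3.1 does concede that the short pre-period limits testing of parallel trends. It does not mention the loss of power.

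**Conclusion.** The concern holds. The stated 81% is correct for an unadjusted comparison of post-period means and does not apply to the primary estimate. For β₃, power to detect 3.5 points is about 28% with 17 pre-period women per arm, and 32–36% if the pre-period runs 10–12 weeks. The study would miss a true effect of the planned size about seven times in ten in the first case and about two times in three in the second.

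This rests on SD 6.5 as the residual SD, different women in each period, independence, and no attrition. Departures from the last two would reduce power further; only a large fall in residual SD would raise it materially. The 91% is likewise a post-only figure, and its DiD replacement is less certain because the pre-period count and the exact model matter. The correction to 44% is a matter of consistency. The primary figure must be corrected before the study is described as adequately powered.

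**What to change.** - In Section 2.12, the Abstract and Section 3.1, report the precision of β₃: SE about 2.5, 95% CI about ±5 points, about 28% power for 3.5 points, and a detectable difference of about 7 points. State the assumptions (independent women, no attrition, no block-by-period variation).
- Reconcile the pre-period length across the Abstract and Sections 2.4, 2.12 and 3.1, or give the 28–36% range until that is done.
- Say that 81% applies only to an unadjusted post-period comparison, and remove the claim in Section 3.1 that the sample suffices at that power.
- Say that extending the post-period cannot raise power above about 35% while the pre-period has 17 women per arm.
- Recalculate the 91% and 44% figures for the DiD models specified, or label them as post-only.
- Present the effectiveness result as an estimate with its confidence interval, and state that a non-significant β₃ will not be read as absence of effect.

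The cost is text changes and a much less favourable stated power; no additional women are required. Reaching 80% power for β₃ would instead take 4 × 6.5² × (2.80/3.5)² ≈ 109 women in each of the four arm-by-period cells, against 17 and 56 now, so restating the precision is the practical course.

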### Study period

2.4

The study comprises a pre-intervention observation period (March–May 2026, approximately 10–12 weeks) and a post-intervention period (May–November 2026, approximately 26 weeks), encompassing the July–October seasonal peak in stillbirths (5.2–5.6 per block per month). Data collection will be completed by December 2026.

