#### Primary effectiveness outcome

2.8.1

The primary effectiveness outcome will be the mean Edinburgh Postnatal Depression Scale (EPDS) total score (continuous, range: 0–30) at Day 60 postpartum (±2 days), measured by an independent study nurse (15). The EPDS was selected as the primary outcome on the basis that the primary target of C-COMPASS is the prevention of pathological depressive disorder following stillbirth, rather than grief resolution *per se*, a longer-term outcome beyond the scope of this first evaluation. The potential overlap between grief and depressive symptoms in the early postpartum period is acknowledged; this is addressed within the study design by the concurrent administration of the Brief Grief Questionnaire (BGQ) as a secondary outcome, enabling exploratory analysis of the relationship between grief and depression constructs in this population. The EPDS has been used in perinatal loss populations and validated in Indian perinatal settings (16, 17), and its use as the primary outcome enables direct comparison with the closest available LMIC analogue and alignment with NHM mental health referral thresholds.

Outcome assessment will be scheduled at Day 60, after the ASHA's Day 42 visit, to ensure a minimum three-day separation between the final C-COMPASS contact and outcome measurement, thereby minimising response priming and maintaining assessor independence. The EPDS captures symptoms over the preceding seven days; thus, administration at Day 60 reflects the post-intervention steady state. This timing is consistent with the original validation of the EPDS at 6–8 weeks postpartum (15).

Where Verbal Autopsy (VASA) is conducted for the same participant, EPDS, SDS, and BGQ will be administered first, preferably on a different day. If same-day administration is unavoidable, outcome measures will be completed prior to VASA to minimise recall-induced emotional bias.

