Bereavement care after stillbirth in high-income countries has been substantially developed over the past two decades. Guidelines from the International Stillbirth Alliance, the ACOG toolkit, and the SANDS bereavement framework provide detailed protocols for communication at the time of loss, memory-making support, and specialist psychological follow-up (5). These models are delivered by bereavement midwives, perinatal mental health specialists, and dedicated follow-up clinics, resources that do not exist and cannot be assumed in rural district hospitals in Haryana. They were not designed for LMIC delivery, and direct adaptation has consistently failed to produce implementable models for low-resource frontline settings. The closest analogue in the Indian context is the Thinking Healthy Programme, which trained community health workers to deliver a cognitive behavioural intervention for perinatal depression, but this was developed for postnatal depression after live birth, not perinatal loss, and required a 10-day training programme and structured supervision that exceeds what is feasible within routine NHM operations (22). C-COMPASS occupies a distinct and underserved position: it is the first protocol designed specifically for post-stillbirth care, delivered through the community health worker infrastructure that already exists at scale, with a training burden and documentation requirement calibrated to real ASHA capacity. The 3-Circle Healing Model at its core: Heart, Mind, Support, was developed and validated through the SHRiSTI co-design process, not translated from a Western psychotherapy framework. This distinction matters both scientifically and practically: an intervention designed for its delivery context is more likely to achieve fidelity, acceptance, and sustainability than one adapted from a structurally different system. Globally, C-COMPASS is distinct in three ways that no existing post-stillbirth protocol combines: it is delivered through a cadre of community health workers (ASHAs) who are trusted members of the same communities they serve; it provides structured grief counselling grounded in a co-designed indigenous healing framework (the 3-Circle Model) rather than an adapted Western psychotherapy protocol; and it operates within and is evaluated as part of a functioning public health system, making its findings directly transferable to government programme adoption rather than requiring a separate scale-up translation phase. Finally, it is worth noting that the concentration of enrolment in the July–October post-intervention period, which corresponds to the seasonal peak in stillbirths documented in SHRiSTI surveillance data, is expected to support timely achievement of the target sample size within the December 2026 data collection deadline, a pattern consistent with published evidence on heat-associated increases in stillbirth risk during peak temperature months in South Asian settings (27).

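### The May–November 2026 accrual window, the Day 60 primary outcome and the December 2026 close do not fit together, and the extension meant to absorb 10% attrition runs past the same close

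*Protocol article*

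**What the plan says.** All references are to the protocol article.

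- **Section 2.4 (Study period)** gives a "pre-intervention observation period (March–May 2026, approximately 10–12 weeks") and a "post-intervention period (May–November 2026, approximately 26 weeks"). It then states: "Data collection will be completed by December 2026".
- **Section 2.8.1 (Primary effectiveness outcome)** takes the EPDS "at Day 60 postpartum (±2 days), measured by an independent study nurse".
- **Section 2.12 (Sample size)** says that "the expected enrolment rate is approximately 9.2 women per arm per month". From this it derives about 17 women per arm over an 8-week pre-period and about 56 per arm over a 26-week post-period. It requires at least 55 per arm and quotes 81% power at 56. For the anticipated 10% attrition it says only that "the post-intervention data collection period may be extended to ensure a minimum effective sample size of 56 women per arm". It also reports a "seasonal peak during July–October (5.2–5.6 per block per month").
- **Section 3 (Discussion)** relies on that peak for "timely achievement of the target sample size within the December 2026 data collection deadline".

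**The concern.** A woman contributes to the primary analysis only if her Day 60 visit takes place, so accrual must stop about two months before data collection does. Section 2.4 leaves about one month between the end of a November accrual period and the end of December. The only provision against attrition is a longer post-period, which pushes the last Day 60 visits further beyond the same date. Nothing in the article moves the December close or says which statement gives way.

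At stake is the stated sample size. If the close holds, late-enrolled post-period women have no primary outcome because of the calendar, and at the planning rate the evaluable number falls below the plan's own minimum of 55 per arm. If the extension is used, the December 2026 dates in sections 2.4 and 3 are wrong.

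**Working it through.** **Inputs.** Difference 3.5, SD 6.5, two-sided alpha 0.05, 9.2 women per arm per month (2 blocks × 4.6), 26 weeks and 10% attrition (section 2.12); Day 60 ±2 (section 2.8.1); December 2026 close and 10–12 week pre-period (section 2.4).

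**Assumptions.** The close is 31 December, the latest reading. The article gives no day in March or May. I take 1 May as the earliest post-period start. I also take 10–24 May, which follows from a pre-period of 10–12 weeks starting on 1 March. The start date counts as the first day; counting otherwise moves the end dates by one day.

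**1. The plan's own figures.**
- n = 2 × (1.96 + 0.8416)² × 6.5² / 3.5² = 54.1, so 55 per arm. This agrees.
- Power = Φ[3.5 / (6.5 × √(2/n)) − 1.96]. At n = 56 this is Φ(0.889) = 81.3%. This agrees.
- Accrual: 9.2 × 26 × 12/52 = 55.2 (stated as about 56); 9.2 × 8 × 12/52 = 17.0. The 56 is therefore all expected stillbirths, with no attrition removed.

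**2. Last usable stillbirth date.** 31 December − 60 days = 1 November. At the −2 day limit, 31 December − 58 days = 3 November.

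**3. The 26-week post-period without extension.**

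| Start | Accrual ends | Last Day 60 |
|---|---|---|
| 1 May | 29 October | 28 December 2026 |
| 10 May | 7 November | 6 January 2027 |
| 24 May | 21 November | 20 January 2027 |

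**4. The extension.** 56 / 0.9 = 62.2. Enrolling 62 leaves 55.8 evaluable, so 63 are needed. 63 / 9.2 = 6.85 months, or 29.7 weeks.

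| Start | 63 enrolled by about | Last Day 60 about |
|---|---|---|
| 1 May | 24 November | 23 January 2027 |
| 10 May | 3 December | 1 February 2027 |
| 24 May | 17 December | 15 February 2027 |

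**5. What is evaluable if the close is kept.** I count stillbirths up to 1 November and multiply by 0.9. The seasonal version takes 5.4 per block per month in July–October, the middle of the stated range. It sets the other months so that the mean stays 4.6 (assumed to be an annual mean): (12 × 4.6 − 4 × 5.4) / 8 = 4.2.

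| Start | Planning rate: enrolled → evaluable (power) | Seasonal rate: enrolled → evaluable (power) |
|---|---|---|
| 1 May | 55.5 → 50.0 (77%) | 60.3 → 54.3 (80%) |
| 10 May | 52.8 → 47.6 (75%) | 57.8 → 52.1 (78%) |
| 24 May | 48.7 → 43.8 (71%) | 54.0 → 48.6 (76%) |

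Stopping at 3 November instead adds at most about half a woman per arm.

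**6. Pre-period.** The same 10% applied to 17 leaves 17 × 0.9 = 15.3, about 15 per arm.

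**The case against.** There are four fair replies.

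- **A 1 May start fits.** It pairs with the 8-week pre-period of sections 2.12 and 3.1, and all Day 60 visits of a 26-week period then fall just inside December. This stands. The January dates for an unextended period depend on the 10–12 weeks of section 2.4 and on my assumed 1 March start. The fit has only a few days' slack, however, and leaves no room for the extension.
- **The plan counts on the July–October peak.** This also stands, and it is why the seasonal column is shown. It closes much of the gap from a 1 May start, where about 54 evaluable is one short of the minimum.
- **The extension clause is permissive, so it could override the date.** That is a possible reading, but the clause has no end date and the Discussion treats December 2026 as a deadline. The passages still need reconciling.
- **A calendar cut-off falls on both arms alike.** Agreed. The demonstrated cost is precision, and no bias is shown.

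A reader might infer that 56 evaluable women per arm are unattainable. The article does not support that. With a start on exactly 1 May, peak rates of 5.4–5.6, all other months at the full 4.6 and every woman consenting, about 56–58 would be evaluable by the close. That is an optimistic combination, because 4.6 is the overall mean and so already includes the peak, but it is not impossible. Moving the close would also deliver the number.

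**Conclusion.** The point holds as a contradiction of dates and a missing attrition allowance. An accrual period reaching into November, a Day 60 outcome and a December 2026 close cannot all stand, whatever the accrual rate. At the planning rate, the extension and the deadline cannot both stand either.

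The loss is moderate. Against the stated 81%, power by the plan's own two-group formula is 71–77% at the planning rate and about 76–80% with the seasonal peak, depending on the start date in May. These figures rest on a 31 December close, the assumed start dates, 10% attrition and full consent. Section 2.5 makes consent and reachability conditions of entry, and the article gives no rate for either, so any refusal lowers the numbers further. The sample size formula reproduces. Whether a two-group formula suits the interaction term that will be tested is a separate question and plays no part here.

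**What to change.** Choose one of two courses and make sections 2.4, 2.12 and 3 agree.

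1. **Keep the December 2026 close.** State about 1 November 2026 as the last eligible stillbirth date and remove the extension clause. Restate the evaluable post-period sample and power after 10% attrition: about 50 per arm and 77% at the planning rate from a 1 May start, with the seasonal range and the effect of a later start shown. This costs only wording and a less favourable figure.
2. **Move the close of Day 60 data collection into 2027.** End-January suits a 1 May start with full extension, or an unextended post-period from any of the start dates above. Mid-February is needed for full extension from a later May start. Give the extension clause a matching end date and an enrolment target of 63 per arm. This costs about one more month of nurse follow-up, or about six to seven weeks for the mid-February close.

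Under either course, state the calendar start of the post-period, settle the pre-period length (8 or 10–12 weeks), and apply the 10% attrition to the pre-period too, so that 17 per arm becomes about 15. The Abstract and section 3.1 repeat the sample size and power and should follow.
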